## Interventions

### The interventions will be launched in September 2016 and last for 28 months, until November 2018 (end of the academic year when the girls who attend school are expected to complete grade 9). In the control arm, girls will be offered some writing materials (exercise books, pencils and pens) as an incentive to participate. This is not likely to be sufficient to have any effect on the primary or secondary outcomes. Apart from this, only standard school and health services will be offered. The interventions will be delivered through personnel in the school and the health system to facilitate potential scale-up in Zambia and similar contexts.

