## Outcomes

### *Primary outcomes:*

- incidence of births within 8 months of the end of the intervention period;
- incidence of births before girls’ 18^th^ birthday;
- proportion of girls who sit for grade 9 exam.

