## Sample size

The sample size is estimated based on the primary outcomes “incidence of births within 8 months of the end of the intervention period” (average age expected to be 17.5 years), “incidence of births before girls’ 18^th^ birthday” and “proportion of girls who sit for grade 9 exam”. We used the 2010 census age-specific estimates of the proportions of 17 and 18 year old girls who ever given birth in the study districts to estimate the proportions in the control arm. The census indicates that 22% of 17 year old and 35% of 18 year old girls in the study districts had ever given birth. Based on this we assume that 27% of girls in the control arm will have given birth before their 18^th^ birthday.

All estimates below have been increased with 10% to compensate for a possible loss to follow up. The sample-size for this cluster-randomized controlled trial was calculated using PASS 14 (NCSS Statistical Software, Utah, US).

*Assumptions for sample size required to measure the primary outcome “birth within 8 months of the end of the intervention period” (*when the average age will be 17.1 years)

| **Parameter** | **Assumed level** | **Comment** |
| --- | --- | --- |
| Incidence of births in control group | 0.06 | Eight months after the end of the intervention period the girls will be on average 17.1 years and we assume that 15% of them will have given birth. This corresponds to an average incidence rate of (15%-3%)/2= 6% over this 2 year period. |
| Effectiveness of combined intervention vs control | -40% | i.e. incidence in combined intervention arm assumed to be 0.036 |
| Cluster size | 28 | See assumptions for the outcome “incidence of births before girls’ 18th birthday” |
| Person years per cluster | 56 | If 28 participants are followed up for 2 years, there will be 56 person years |
| Coefficient of variation (k) | 0.2 | The ICC was 0.00737 for “ever pregnant” after cash transfer trial in Malawi. This corresponds to k=0.20 when the total proportion who have given birth by this time is 0.15 |
| Z_1_ (acceptable alpha error level) | 1.96 |  |
| Power for comparison of combined intervention vs control | 90% | We need 36 combined clusters vs 36 control clusters to have 90% power detect the assumed difference. The PASS function for proportions indicates that with 63 combined clusters, we will have >90% power with 30 control clusters. |
|  |  |  |

*Assumptions for sample size required to measure the primary outcome “birth before 18^th^ birthday”*

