## Statistical methods

The outcomes will be captured in binary, continuous or a time-to-event variables. Continuous variables that are right skewed will be log-transformed to obtained more symmetrical distributions. We will correspondingly employ Poisson regression or General linear models (GLM) of the binomial family with a log link (estimating risk ratios or RRs) and identity link (estimating absolute risk reduction), linear regression (estimating average effect or mean increase or decrease) or survival analysis using Cox regression. Each method will take account of the design effect of the clustering.

The data will be analysed with Stata (Stata Corporation, TX, USA) statistical software. We will compare outcomes between the three arms: the economic arm vs. the control arm, the combined arm vs the control arm, and the economic arm vs the combined intervention arm. Analyses will be by intention-to-treat (ITT), that is all participants, irrespective of whether they actually agree to the intervention allocated to them, will be included in the analysis according to the intervention arm the cluster they live in was allocated to. The Intracluster correlation (ICC) will be reported for all primary and secondary outcomes.

The primary outcomes will be measured in the final survey in February 2020 based on the participants’ responses to the questions “Have you ever given birth?” and “If yes, on which date and which year did you give birth?”. Reported childbearing before July 2019 will be recorded as “birth 8 months after end of the intervention period”. Girls who report a date of childbearing preceding their 18^th^ birthday, will be recorded as having “birth before 18^th^ birthday”. Girls who are married at the start of the intervention, will be excluded from the analysis of proportion of girls ever married/cohabiting before their 16^th^ or 18th birthday.

Descriptive statistics, such as means or medians and standard deviation or interquartile range will be used to describe continuous variables (the choice depending on the distributions). For categorical variables, frequencies and percentages will be calculated.

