| Recruitment and baseline survey |  |  |  |  | X | X | X | X | X |  |  |  |  |  |  |  |  |  |  |  |  |  |  |  |  |  |  |  |  |  |  |  |  |  |  |  |  |  |  |  |  |  |  |  |  |  |  |  |  |  |  |  |  |  |  |  |  |  |  |  |  |
|  |  |  |  |  |  |  |  |  |  |  |  |  |  |  |  |  |  |  |  |  |  |  |  |  |  |  |  |  |  |  |  |  |  |  |  |  |  |  |  |  |  |  |  |  |  |  |  |  |  |  |  |  |  |  |  |  |  |  |  |  |  |
| **Randomization** |  |  |  |  |  |  |  |  | X |  |  |  |  |  |  |  |  |  |  |  |  |  |  |  |  |  |  |  |  |  |  |  |  |  |  |  |  |  |  |  |  |  |  |  |  |  |  |  |  |  |  |  |  |  |  |  |  |  |  |  |  |
| **Community/parent meetings to provide information about allocation after randomization** |  |  |  |  |  |  |  |  | X | X | X |  |  |  |  |  |  |  |  |  |  |  |  |  |  |  |  |  |  |  |  |  |  |  |  |  |  |  |  |  |  |  |  |  |  |  |  |  |  |  |  |  |  |  |  |  |  |  |  |  |  |
|  |  |  |  |  |  |  |  |  |  |  |  |  |  |  |  |  |  |  |  |  |  |  |  |  |  |  |  |  |  |  |  |  |  |  |  |  |  |  |  |  |  |  |  |  |  |  |  |  |  |  |  |  |  |  |  |  |  |  |  |  |  |
| **Economic component** |  |  |  |  |  |  |  |  |  |  |  |  |  |  |  |  |  |  |  |  |  |  |  |  |  |  |  |  |  |  |  |  |  |  |  |  |  |  |  |  |  |  |  |  |  |  |  |  |  |  |  |  |  |  |  |  |  |  |  |  |  |
| UCT |  |  |  |  |  |  |  |  |  |  | X | X | X | X | X | X | X | X | X | X | X | X | X | X | X | X | X | X | X | X | X | X | X | X | X | X | X |  |  |  |  |  |  |  |  |  |  |  |  |  |  |  |  |  |  |  |  |  |  |  |  |
| Payment of school fees |  |  |  |  |  |  |  |  |  |  |  |  |  |  | X |  |  |  |  |  |  |  |  |  |  |  | X |  |  |  |  |  |  |  |  |  |  |  |  |  |  |  |  |  |  |  |  |  |  |  |  |  |  |  |  |  |  |  |  |  |  |
| **Community component** |  |  |  |  |  |  |  |  |  |  |  |  |  |  |  |  |  |  |  |  |  |  |  |  |  |  |  |  |  |  |  |  |  |  |  |  |  |  |  |  |  |  |  |  |  |  |  |  |  |  |  |  |  |  |  |  |  |  |  |  |  |
| Selection of teachers, CHWs, youth peer educators |  |  |  |  |  |  |  |  | X | X |  |  |  |  |  |  |  |  |  |  |  |  |  |  |  |  |  |  |  |  |  |  |  |  |  |  |  |  |  |  |  |  |  |  |  |  |  |  |  |  |  |  |  |  |  |  |  |  |  |  |  |
| Training of teachers and CHWs and trial supervisors |  |  |  |  |  |  |  |  |  | X |  |  |  |  |  |  |  |  |  |  | X |  |  |  |  |  |  |  |  |  |  |  |  |  |  |  |  |  |  |  |  |  |  |  |  |  |  |  |  |  |  |  |  |  |  |  |  |  |  |  |  |

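### The stated intervention length, its end month and the July 2019 birth cut-off cannot all hold, and the 8-month birth outcome is probably coded over about 7 months

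*Protocol*

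**What the plan says.** Four parts of the protocol bear on this outcome.

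- **Definition.** Under Primary outcomes, the first outcome is the "incidence of births within 8 months of the end of the intervention period". The protocol summary defines it in the same way.
- **Intervention period.** The Interventions section states: "The interventions will be launched in September 2016 and last for 28 months, until November 2018". It explains the end month as the "end of the academic year when the girls who attend school are expected to complete grade 9".
- **Schedule.** The Participant timeline and Appendix 1 (the cash-transfer row under "Economic component") mark unconditional cash transfers every month from September 2016 to November 2018. Both also mark a community meeting in November 2018. Neither marks any cash transfer or community meeting in December 2018.
- **Coding rule.** Statistical methods says: "Reported childbearing before July 2019 will be recorded as" an event, under the label "birth 8 months after end of the intervention period".

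The change log at the end of the protocol does not mention the intervention's end date or this cut-off, so the contradiction lies in current text.

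**The concern.** The coding rule in Statistical methods is the only operational rule that the protocol gives for this primary outcome, and it fixes a calendar date. If that date is not 8 months after the end of the intervention, the variable that is analysed is not the outcome that was defined. A girl who gave birth in July 2019 could meet the definition and still be coded as a non-event.

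The text also leaves more than one defensible cut-off. Participants are not blinded, and the choice of window for a primary outcome should not be left open until the data are in hand.

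**Working it through.** **Inputs.** Launch in September 2016, length 28 months, end in November 2018 (Interventions); monthly cash-transfer marks (Participant timeline and Appendix 1); 8-month definition (Primary outcomes); births before July 2019, so the last counted day is 30 June 2019 (Statistical methods); planned rates and cluster assumptions (Sample size).

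**Step 1: length.** The cash-transfer marks number 4 in 2016, 12 in 2017 and 11 in 2018: 4 + 12 + 11 = 27 months. Leaving November 2018 out gives 26. The stated 28 does not reproduce with a September start and a November end. Counted from 1 September 2016, 28 full months end on 31 December 2018.

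**Step 2: cut-off.** For each possible end date:

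| End of intervention | Length from 1 Sept 2016 | Last day of 8-month window | Months covered by the coding rule |
|---|---|---|---|
| 31 Oct / 1 Nov 2018 | 26 months | 30 June 2019 | 8 |
| 30 Nov 2018 | 27 months | 31 July 2019 | 7 |
| 31 Dec 2018 | 28 months | 31 Aug 2019 | 6 |

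No row satisfies the stated length, the November end and the 8-month window together. The middle row is the one that matches the timelines.

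**Step 3: births affected.** The sample size section derives the control rate thus: "This corresponds to an average incidence rate of (15%-3%)/2= 6% over this 2 year period". One month at that rate is 0.06 / 12 = 0.005, or 0.5 births per 100 girls. With about 1,000 girls planned in the control arm, that is about 5 births. For the combined arm, "i.e. incidence in combined intervention arm assumed to be 0.036": 0.036 / 12 = 0.003, and 0.003 × 1,950 = 5.85, about 6 births. At the planned rates the missing month has the same rate ratio as the rest, 0.036 / 0.06 = 0.60.

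**Step 4: share of the window.** Launch to 30 June 2019 is 34 months. Launch to 31 July 2019 is 35 months. The shortfall is 1 / 35 = 2.9%. Dividing by the sample size table's 24 months would give 1 / 24 = 4.2%, but 24 months is not the length of the coded window.

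**Step 5: power.** The usual cluster formula for rates is

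c = 1 + (z₁ + z₂)² × [(λ₀ + λ₁)/y + k²(λ₀² + λ₁²)] / (λ₀ − λ₁)²

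with λ₀ = 0.06, λ₁ = 0.036, k = 0.20, z₁ = 1.96, 90% power and y = 56 person-years per cluster (28 girls × 2 years).

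- The protocol's figure reproduces: c = 35.85, rounded up to the stated 36. Power at 36 vs 36 clusters is 90.1%.
- With one month taken off the assumed 2 years, y = 28 × 23/12 = 53.67 and power is 89.0%.
- With the 35- and 34-month windows that the dates imply, and the same rates, power is 97.0% and 96.6%.

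The cluster count is therefore sound on its own assumptions. The error lies in the dates.

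**The case against.** The strongest reply is that the protocol gives months and not days. If the intervention runs only up to the start of November 2018, births before July 2019 give exactly 8 months, and an end date within November gives between 7 and 8. This stands to the extent that 7 months is the likely reading and not a certain one. It does not remove the contradiction. An end at the start of November makes the intervention 26 months long, further from the stated 28, and it conflicts with the cash transfer and community meeting marked in November 2018. Some text has to change under every reading.

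A second reply is that the effect is small and the same in all arms. This stands. The cut-off does not depend on allocation, power moves by about one percentage point or less, and birth dates are asked for, so the outcome can be recomputed at another cut-off.

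Several stronger readings are tempting, but the documents do not support them:

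- *Only 6 months are covered.* This needs an end on 31 December 2018. The Interventions section names November explicitly and ties it to the academic year, and neither timeline has a December 2018 cash-transfer mark. A miscount in the figure 28 is the simpler explanation.
- *Rates are biased downwards because person-time runs longer than the birth count.* Nothing in Statistical methods separates the two dates.
- *The result departs from the registered outcome.* No registry record is at hand. The comparison can be made only with the protocol's own definition.
- *The lost share is larger because older girls have higher birth rates.* The protocol gives no rate for mid-2019, and a higher monthly rate cannot be set against a total computed at the lower one.

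**Conclusion.** The contradiction is real: 28 months, an end in November 2018 and a cut-off before July 2019 as the 8-month mark cannot all be true. If November 2018 was a full month of support, as both timelines show, the rule covers about 7 months and drops July 2019 births that meet the definition. The size is about 0.5 births per 100 girls at the planned control rate, or about 3% of the window from launch.

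This rests on an end date of 30 November 2018, which the timelines suggest but no section states, and on a constant rate of 0.06 per year. A reader might infer that the trial comparison is biased. The documents do not support that, because one calendar cut-off applies to all arms. What is affected is the definition of a primary outcome, its event count and, slightly, its power. It should be fixed, but it does not threaten the trial's conclusions.

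**What to change.** 1. In the Interventions section, state the actual calendar date on which the intervention ended, and reconcile the length of 28 months and the timelines with it. Which figure is correct is for the investigators to establish from their records.
2. In Statistical methods, replace the July 2019 rule with a cut-off equal to that date plus 8 calendar months. If the end date is 30 November 2018, births up to and including 31 July 2019 count.
3. State that each girl's person-time for this outcome ends no later than the same cut-off.

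The cost is a sentence or two in each of the two sections. The date of birth of the child is already asked for, and the final survey falls in 2020, after every candidate cut-off, so no new data are needed. The change should be made and dated before outcome data are compared by arm.

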|  | UCT | |  |  |  |  |  |  |  |  | X | X | X | X | | X | X | X | X | X | X | X | X | X | X | X | X | | X | X | X | X | X | X | X | X | X | X | X |  | |  |  |  |  |  |  |  |  |  |  |  |  | |  |  |  |  |  |  |  |  |  |  |  |  |
|  | Payment school fees | |  |  |  |  |  |  |  |  |  |  |  |  | | X |  |  |  |  |  |  |  |  |  |  |  | | X |  |  |  |  |  |  |  |  |  |  |  | |  |  |  |  |  |  |  |  |  |  |  |  | |  |  |  |  |  |  |  |  |  |  |  |  |
|  | Youth club meetings | |  |  |  |  |  |  |  |  | X | X | X |  | | X | X | X |  | X | X | X |  | X | X | X |  | | X | X | X |  | X | X | X |  |  |  |  |  | |  |  |  |  |  |  |  |  |  |  |  |  | |  |  |  |  |  |  |  |  |  |  |  |  |
|  | Community meetings | |  |  |  |  |  |  |  |  | X |  | X |  | | X |  | X |  | X |  | X |  | X |  | X |  | | X |  | X |  | X |  | X |  | X |  | X |  | |  |  |  |  |  |  |  |  |  |  |  |  | |  |  |  |  |  |  |  |  |  |  |  |  |
| Assessments | Baseline interview | |  |  | X | X | X | X |  |  |  |  |  |  | |  |  |  |  |  |  |  |  |  |  |  |  | |  |  |  |  |  |  |  |  |  |  |  |  | |  |  |  |  |  |  |  |  |  |  |  |  | |  |  |  |  |  |  |  |  |  |  |  |  |
|  | Follow-up contacts | |  |  |  |  |  |  |  |  |  | X | X | X | |  |  |  | X | X | X | X |  | X | X | X | X | |  |  | X | X | X | X |  |  | X | X | X | X | |  |  | X | X | X | X |  |  | X | X | X | X | |  | X | X | X | X |  |  |  |  |  |  |  |
|  | Final survey | |  |  |  |  |  |  |  |  |  |  |  |  | |  |  |  |  |  |  |  |  |  |  |  |  | |  |  |  |  |  |  |  |  |  |  |  |  | |  |  |  |  |  |  |  |  |  |  |  |  | |  |  |  |  |  |  | X | X | X | X | X |  |

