## Recruitment

Research assistants will between March and June 2016, i.e. in terms 1 and 2, visit selected schools (with grade 7) and inform girls who are enrolled in grade 7 about the study. The parents/guardians of girls in grade 7 will be invited to an information meeting. If their daughter is < 18 years, they will be asked to give consent to her participation in the trial. A few days later the research assistants will return to the school and ask girls to consent (if they are ≥18 years) or assent (if they are younger than 18 years and their parents or legal guardians have consented) to participation. Those who consent/assent and participate in the baseline survey will be enrolled.

Repeat visits will be made to the school to give girls who are absent on the day of the visit a chance to be enrolled.

Addresses and mobile phone numbers of the girl (if any), parents/guardians and close relatives or neighbours will be recorded when consent/assent is obtained. The girl will be asked to specify the preferred telephone number that can be used to make phone-based follow-up contacts with her.

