## Randomization and blinding/masking

Randomization will take place in July 2016, after recruitment and baseline interviews. Randomization will be stratified by district. For each of 6 areas (each area corresponding to 2 districts) approximately 1000 allocations of the clusters will be computer-generated by an independent scientist tasked by CISMAC. Each allocation will be numbered. We will organize six randomization ceremonies where schools will be randomly allocated to one of the three trial arms. Officials from the study districts, head teachers and PTA chairpersons of the trial schools and chiefs will be invited to be present, and others, including community members, will be welcome to come too. Tickets will be drawn from a box with numbers corresponding to a specific allocation of clusters to the three arms.

There will be no blinding of participants, but the team doing the final survey will be independent from the intervention delivery and efforts will be put in place to keep them unaware of the intervention/control status of respondents. Biannual follow-up contacts with the participants and the final surveys will be conducted by an independent team of research assistants, most of them located in Lusaka.

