## Data collection methods

A baseline interview will be conducted as part of the recruitment. As part of the trial there will be short phone-based or physical follow-up contacts with all the participants twice per year to update contact details and sociodemographic information. A final follow-up survey will also be conducted. Data will be captured electronically using tablets during face-to-face interviews and using tablets or computers during phone-based surveys and follow-up contacts.

Qualitative and quantitative process evaluation will take place throughout the intervention period in order to understand how the intervention works. Such monitoring activities will also allow identification of needs to make adjustments to the intervention delivery (the intervention will be adaptive [54]). In addition, incentivized lab experiments will be included.

We will collect information about the location and size of pre-randomization non-consenting schools, and information about age and village of girls who do not assent or whose guardians to do not consent, in order to assess the likely degree and direction of selection bias in the study

All the tools will be translated to Tonga, Nyanja, Lenje and Bemba, the dominating local languages in the study districts, and then back-translated to ensure that the content is maintained. Interviews will be conducted in English, Tonga, Nyanja, Lenje or Bemba depending on what the participant prefers.

##

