| **Follow-up contacts** | All the girls in the intervention and control arms will be contacted every 6 months to update contact information and ask questions about school attendance, employment, marital status and childbearing, health care seeking, and whether they have received the cash transfers and/or participated in the youth club meetings. To monitor adverse events that can be attributed to the trial, girls will also be asked whether they have experienced problems due to their participation in the trial. In the fourth follow-up interview (taking place during the first two quarters of 2018) additional questions will be asked about communication about sexual and reproductive health issues.  In order to make it easier for the participants to respond to the more sensitive questions, Audio Computer Assisted Self-Interviewing (ACASI) will be used for questions 69-82. This will be done by giving the participants headsets so they can listen to the questions being read to them and they will be given privacy to fill in the correct responses on the tablets themselves. ACASI-technology has been shown to increase participants’ perceptions of privacy and anonymity and it appears to reduce social desirability bias [52, 53]. In addition, the item count technique [54, 55] will be used. This is an indirect questioning technique where the participants indicate how many of a set of statements are true for them, rather than whether each of the individual statements are true or false. If the girl cannot be found at school or at home at the time of the follow-up interview, call centre research assistants will attempt to reach her by phone.  In the third follow-up round we experienced challenges in several of the control schools with finding the participants because many of them were not in school any more. In order to motivate the participants to come to the school to be interviewed, we will increase the transport allowance provided for control participants from K20 to K50 per interview in 2018 and further to K75 in 2019 and K100 for the final interview in 2020. For the participants in the intervention arms, we do not think it is necessary to provide such an allowance during the period when they are receiving economic support, and thus a transport allowance of K75 / K100 will only be provided for interviews in 2019 and 2020. The participants will then have finished grade 9 and we expect a large proportion of them to move away from the study areas, either to go to grade 10 in a secondary school or to get married or work. This implies that they will either have to travel to come back for interviews and need to be compensated for the costs and time that this requires. And for those that move far away, they will have to keep their phone number active for us to be able to interview them over the phone and many of them will also have to call us to inform us when they will be available, and thus the compensation should be sufficient to cover the costs of this.  Around the time of the fourth follow-up interviews with the RISE participants in the first half of 2018, their parents/guardians will also be invited to come to parent meetings where they will be asked take part in an interview. Parents/guardians who do not come to the meeting will be sought at home. The questions in the parent interview pertain to expenses they have had in the previous 6-12 months related to food, education, health care and other expenditures, and about their attitudes to early marriage, early childbearing, contraceptive use and education. A travel allowance of K50 will be offered to the guardians who are interviewed.  The research assistants will be asked to take selfies of themselves with the participants to document that they have interviewed the correct participants. The trial participants in most cases live far away from each other and the research assistants who do the interviews travel alone (or with a driver) on a motorbike to find the participants. Thus, even if there is a supervisor who makes unannounced monitoring visits to observe the research assistants twice per month, most of the interviews are done without other project staff being able to observe them. We are worried that some of the research assistants may be tempted to manufacture some of the interviews, particularly when it is difficult to find participants because they have moved (which is the case for an increasing proportion of our participants). We expect that such pictures will make fabrication of interviews less likely. |

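### The marriage analysis excludes girls by status at the start of the intervention, about two months after open allocation, instead of status before randomisation

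*Protocol*

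**What the plan says.** The exclusion rule is in the Statistical methods section: "Girls who are married at the start of the intervention, will be excluded from the analysis of proportion of girls ever married/cohabiting" before the 16th or 18th birthday. The same section sets an intention-to-treat analysis of all participants in the arm to which their cluster was allocated.

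The dates are fixed elsewhere in the protocol:

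- **Recruitment:** "Research assistants will between March and June 2016, i.e. in terms 1 and 2, visit selected schools". Under Data collection methods, "A baseline interview will be conducted as part of the recruitment".
- **Randomization and blinding/masking:** "Randomization will take place in July 2016, after recruitment and baseline interviews". Allocation is drawn at ceremonies open to the community, and participants are not blinded.
- **Interventions:** "The interventions will be launched in September 2016".
- **Table 1:** after baseline, six-monthly contacts "ask questions about school attendance, employment, marital status and childbearing". In the Participant timeline, the row "Follow-up contacts" is first marked in October 2016.

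The Eligibility criteria admit girls who are already married, so the marriage outcome does need some exclusion rule. Early marriage is a secondary objective, and marriage or cohabitation before 18 is a secondary outcome.

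**The concern.** The cut-off for removing girls lies after randomisation and is defined by the outcome itself. A girl who marries in July–September 2016, once her school's arm has been drawn in public, has the event that the analysis is meant to count. The rule takes her out of both numerator and denominator.

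Marital status on that date could depend on arm. The description of the economic support arm says that the cash is meant to make marriage less pressing for parents and guardians. Families who learn in July or August that support is coming, or is not, might act on it before the first payment. If so, the groups left after exclusion are no longer exactly the groups that were randomised, and the marriage analysis is not the intention-to-treat analysis that the section promises.

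The wording also leaves an analyst without a scheduled record of status on the date named. In addition, the rule refers to married girls, while the outcome is marriage or cohabitation.

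**Working it through.** The protocol states no figure that depends on this rule, so there is none to reproduce. The check is a comparison of dates, followed by an illustration of size.

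**1. Order of events in 2016**

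| Event | Date | Where stated |
|---|---|---|
| Baseline interview | March–June (row runs into July in Appendix 1) | Recruitment; Participant timeline; Appendix 1 |
| Randomisation, in public | July | Randomization and blinding/masking |
| Meetings telling families the allocation | August–October, or July–September | Participant timeline; Appendix 1 |
| Intervention starts; cut-off of the rule | September | Interventions; Participant timeline |
| First follow-up contact | October–December | Participant timeline; Appendix 1 |

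The cut-off is about two months after randomisation. The nearest scheduled records of status are the baseline interview, before allocation, and the first follow-up contact, after the intervention has begun. That the baseline interview records marital status is inferred, because the questionnaire is not shown.

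**2. Girls affected**

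The protocol gives no marriage rate. Assume 2–6% of girls marry per year. Share marrying in the window = annual rate × 2/12:

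- 0.02 × 2/12 = 0.33%; 0.06 × 2/12 = 1.0%.

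The Sample size section plans 31 girls per school, with 31 control schools and 63 per intervention arm:

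- Control: 31 × 31 = 961 girls; 961 × 0.33–1.0% = about 3–10 girls.
- Each intervention arm: 63 × 31 = 1953 girls; 1953 × 0.33–1.0% = about 7–20 girls, if marriage in the window is not affected by arm.

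**3. Effect on the risk ratio**

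Assume three years from randomisation, a risk ratio of 0.75 after the intervention starts, and a window risk ratio *r* for marriages between allocation and start. Let *m* be the annual control rate.

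- Counting every girl from randomisation: RR = [*r* × 2/12 + 0.75 × (3 − 2/12)] / 3 = *r*/18 + 0.7083.
- Under the protocol's rule: RR = 0.75 × (1 − *m*/6) / (1 − *r* × *m*/6).

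| Window RR *r* | Everyone counted | Rule, *m* = 2% | Rule, *m* = 6% | Shift made by the rule |
|---|---|---|---|---|
| 0.5 | 0.736 | 0.749 | 0.746 | +0.010 to +0.013 (towards 1) |
| 0.75 | 0.750 | 0.749 | 0.748 | −0.001 to −0.002 |
| 0.9 | 0.758 | 0.750 | 0.749 | −0.009 (away from 1) |
| 1.0 | 0.764 | 0.750 | 0.750 | −0.014 (away from 1) |

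The shift changes sign close to the point where the window effect equals the later effect, and it is about 0.01–0.015 at the two ends of the range.

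The tipping point differs on the absolute scale, which the protocol also plans to report. At *m* = 6% and *r* = 0.9, the risk difference is 0.1800 − 0.1365 = 0.0435 when everyone is counted and 0.1717 − 0.1287 = 0.0431 (from unrounded values) under the rule, a slight move towards zero.

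**The case against.** The case on the other side is that this is loose wording. The only interview before launch is the baseline, so an analyst might naturally read the start of the intervention as baseline. The record of changes says that the marriage measures became incidence rates in October 2020, and the at-risk set for a rate is commonly settled in a statistical analysis plan, which is not at hand. The effect is also small and touches no primary outcome or sample-size figure. The point about size stands. The point about wording does not remove the problem, because the protocol states a rule with a reference date instead of leaving the matter open, and an analyst who followed it would apply the wrong date.

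The same objections limit how far the point can be taken. A reader might infer four stronger things:

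- **That the rule biases the marriage effect towards zero.** On the risk-ratio scale this needs an announcement effect larger than the later effect of the support itself. Nothing in the protocol argues for that, and with a weaker announcement effect the shift goes slightly the other way.
- **That status in September 2016 cannot be known.** No contact is scheduled then, but an outcome defined by marriage before a birthday needs an age or date at marriage, so status might be reconstructed. That would solve the measurement problem and leave the post-randomisation exclusion in place.
- **That status would be taken from the first follow-up contact, which would widen the window.** Nothing in the protocol says so.
- **That every family knew its arm before the cut-off.** The ceremonies are public, but the two timelines run the information meetings to September or October, so some families may have learned only around or after launch.

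**Conclusion.** The point holds as a small but clear inconsistency. The rule removes events that occur after randomisation, with allocation public, on a status that could depend on arm, and this does not fit the intention-to-treat statement in the same section. It is worth correcting because the principle is plain and the remedy cheap, not because the likely bias is large.

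Its size rests on assumptions: a marriage rate of 2–6% per year (about 0.3–1.0% of girls in the window), a later risk ratio of 0.75 over three years, and a window risk ratio between 0.5 and 1.0. Under these the risk ratio moves by at most about 0.014, and the documents do not settle the direction. Only the marriage outcomes are affected.

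**What to change.** In Statistical methods, replace the reference date. Exclude from the marriage analyses only girls who were married or cohabiting before the date of randomisation, in practice as recorded at the pre-allocation baseline interview, and count every marriage or cohabitation after randomisation as an outcome. Naming cohabitation also brings the exclusion into line with the outcome.

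The cost is a few words and no new data, provided that the baseline questionnaire records marital status, which should be confirmed.

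There is one downside. If baseline-interview status alone is used, marriages between the interview and allocation count as events. That interval is roughly 1–4 months, so at 2–6% per year it holds about 0.2–2.0% of girls (0.02 × 1/12 to 0.06 × 4/12). These marriages precede allocation and cannot depend on it, so they dilute the contrast slightly but not differentially by arm. If marriage dates are available, a sensitivity analysis that also excludes these girls would show whether it matters.
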